### Monitoring

#### Data monitoring

The study will be conducted as a single-center trial. Data monitoring will therefore be performed by the study team, headed by the principal investigator. Due to the small sample size and single-center setting, no data monitoring committee is required.

The study procedures and the collected data are continuously monitored and controlled by the study team. If there are any signs that patients in the intervention group are at risk from the study measures or premature evidence of the inferiority of the control group, the study can be interrupted at any time. Due to the small sample size, no interim analysis is planned.

#### Harms

Unexpected complications will be monitored. Since the CytoSorb adsorber is a tested and approved medical device, such hazards are not to be expected. See the “Early termination of the study” section on provisions for early termination of the study due to safety concerns.

#### Auditing

In addition to the above-described monitoring activities, no specific auditing is required for this single-center trial.

## Ethics and dissemination

### Research ethics approval

This study protocol is approved by the University of Freiburg’s Ethics Committee (EK-FR 21-1470).

### Protocol amendments

All relevant protocol modifications will be submitted to the University of Freiburg’s Ethics Committee for approval. No changes will be implemented before ethical approval.

### Consent or assent

Before being enrolled in the study, written consent will be obtained either from the patient, a relative, or from a legally authorized representative (LAR).

Patients with ACLF eligible for study inclusion may suffer from impaired cognitive capacity, among others, owing to hepatic encephalopathy or acute renal failure. Most patients eligible for inclusion in the CYTOHEP study will not be able to adequately understand the current study and the study interventions, therefore, informed consent must be obtained from a relative or a LAR. When a patient with impaired cognitive capacity is admitted to the Freiburg University Medical Center, as part of a clinical routine and independent from any potential study participation, the medical care team (doctors and nursing staff) will ensure rapid contact with the patient’s relatives or a LAR. In general, relatives can be identified and contacted quickly. If these initial attempts are unsuccessful, the police may attempt to contact them. If the patient has no relatives or they cannot be identified or contacted, a request to appoint a LAR will be made to the local court as soon as possible. The LAR is then informed about the current research project. After regaining consciousness and the ability to give consent before the end of the examination period, the patient is informed again (Table 4).

Table 4 Variants of information on participation in the study

### Confidentiality

The name of the patients is not saved. However, the evaluation of age, sex, and time of admission merely provides a pseudonymization. Pseudonymization of personal data makes it much more difficult to identify the persons concerned and can only be done safely by using a list in which the pseudonym and patient name are combined. Pseudonymization is carried out directly in the raw data before any further processing, so that only the pseudonyms are recognizable in all evaluations. The decryption table is kept separately and protected; only the coordinating investigator and his deputies have access to this list. Participant´s study information will not be released outside of the study without the written permission of the participant, except as necessary for monitoring.

### Access to data

All members of the study team and all researchers involved in data collection, evaluation, and writing of the scientific publication(s) related to this study will have full access to all data collected. There are no contractual agreements with anyone that would limit the access to the data by any means.

### Ancillary and post-trial care

Since there are no harms to be expected resulting specifically from the trial-specific interventions, no special provisions are made for trial-specific ancillary or post-trial care. In this study, CRRT and the Cytosorb adsorber are used within the scope of the intended purpose of the medical products with CE marking. The Cytosorb adsorber is used in the study under the same conditions as in clinical routine, so that no other hazards or risks occur and therefore, according to the MPG (Medizinproduktegesetz), there is no obligation for a specific insurance. The same is true for renal replacement therapy which is used according to established standards as in clinical routine. The additional blood samples in the study are taken via arterial or venous catheters, which are also inserted independently of the study participation, and do not represent a relevant risk; the total amount of blood collected is low. Patients are covered by the hospital’s regular liability insurance. Not all patients randomized to the safety control group without CRRT will require an arterial catheter or a central venous catheter. In these patients, blood samples are taken via peripheral venous punctures. The risk of these additional punctures can be considered very low and they are necessary for guiding treatment in these patients independent of their participation in the trial.

### Early termination of the study

The study may be discontinued at the discretion of the principal investigator or if any of the following criteria are met:
Medical or ethical concernsThe safety of the participants is doubtful or at risk, respectivelyToo many AEs unknown previously (i.e., not previously reported in any similar study or in market use with respect to their nature, severity, and/or duration)Alterations in accepted clinical practice that make the continuation of a clinical trial unwiseEarly evidence of benefit or harm of the experimental interventionDifficulties in the recruitment of patients

In a recent randomized controlled pilot trial in 34 COVID-19 patients on ECMO (CYCOV study), an association between cytokine adsorption and increased mortality has been described [32]. With specific respect to these findings, all patient deaths within the CYTOHEP study will be evaluated continuously and before inclusion of any further patient into the trial, the risk-benefit ratio for continuation of the study will be assessed by the principal investigator. After inclusion of every fifth patient, the principal investigator, the co-principal investigators, and the trial statistician will discuss the risk-benefit ratio for continuation of the study based on the results of the patients included until then and come to a joint decision as to continue or discontinue the study.

Optimal timing of initiation of CRRT in AKI is a matter of ongoing debate. In the CRRT groups of this trial, CRRT will be initiated when patients reach AKI KDIGO grade 3. However, in our hospital, CRRT in AKI in general is initiated later, i.e., not before patients develop life-threatening complications, such as severe hyperkalemia or severe respiratory failure due to volume overload. In patients with ACLF, specifically, there is no clear evidence supporting an early or a late initiation strategy for CRRT. For safety reasons, we will include a third study group without CRRT as a safety control group. Patients randomized to this group will not receive early CRRT as in the other groups but the use of CRRT will be delayed until the development of one or more of the following criteria: a serum potassium level of 6.0 mmol or more per liter, a pH of 7.20 or less due to metabolic acidosis or a serum bicarbonate level of 12 mmol per liter or less, evidence of severe respiratory failure based on a ratio of the partial pressure of arterial oxygen to the fraction of inspired oxygen of 200 or less and clinical perception of volume overload. We will continuously monitor survival, complications, and safety of the treatment in all study groups to be able to detect early any potential harm related to CytoSorb treatment or early initiation of CRRT in comparison to the no CRRT group.

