#### Sample size

In this study, the randomization to the treatment arms CRRT with CytoSorb, CRRT without CytoSorb, and no CRRT will be done with a 1:1:1 ratio. The group with no CRRT is included merely for exploratory analysis of safety aspects and does not affect the power analysis. The sample size calculation is motivated by data from case reports and retrospective case series, according to which serum bilirubin levels in patients with liver failure could be reduced by 50% by adsorption in the CytoSorb adsorber for 72 h [17–20]. We expect a mean of 10 mg/dl serum bilirubin at baseline, no change in control patients, and a reduction to a mean of 5 mg/dl after 72 h in the cytokine adsorption group. The typical range, 1 to 20 mg/dl, implies an expected standard deviation of about 5 mg/dl. This is a conservative estimate, as the inclusion criterion, bilirubin >5mg/dl, was not considered for the calculation. On the basis of a two-group *t*-test with a two-sided significance level of 5%, a sample size of 17 patients in each group yields a power of 80% to detect a difference if it is assumed that the mean serum bilirubin levels after 72 h differ by 5 mg/dl, given a standard deviation of 5 mg/dl in both groups. This is conservative in that we anticipate a lower standard deviation after 72 h in the intervention group. No missing values up to 72 h are expected. Hence, the numbers of patients to be randomized to the three treatment arms are *n*=17:17:17.

In the unexpected event that patients die within the study before reaching the 72-h end point, we will describe an appropriate expansion of enrolment in an amendment to this study protocol.

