### Assignment of interventions

#### Allocation

##### Sequence generation

Allocation to the intervention and control groups is carried out by 1:1:1 randomization, stratified for baseline serum bilirubin level (< 10 mg/dl, ≥ 10 mg/dl) and with blocks of variable length within strata. The block lengths will be documented separately and will not be disclosed to the investigators. Staff not otherwise involved in the trial will provide a computer-generated random list with the allocation sequence for the study groups.

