#### Statistical methods

##### Statistical methods for analyzing primary and secondary outcomes

Confirmatory statistical testing will be restricted to the analysis of the primary outcome, to be followed by descriptive reporting of other trial results**.** Emphasis will be given to reporting of effect estimators with two-sided 95% confidence intervals rather than *p* values, which will be considered statistically significant if below 5% for tests of equality.

In the primary analysis, randomized groups will be compared using a sequential closed test procedure: To guarantee a multiple significance level of 5%, confirmatory statistical testing at nominal significance level *α*=5% will continue until the first non-significant result, followed by descriptive reporting of the results of subsequent analyses. Treatment arms will be compared in the following order: CRRT with CytoSorb versus CRRT without CytoSorb, CRRT without CytoSorb versus no CRRT, CRRT with CytoSorb versus no CRRT.

The effects of CRRT with CytoSorb versus CRRT without CytoSorb with respect to the primary endpoint serum bilirubin level after 72 h will be estimated and tested within a linear regression model, and the two-sided 95% confidence interval will be calculated. The model will include randomized treatment group and continuous baseline bilirubin level as independent variables. Robust standard errors will be used to allow for different error variability in the two treatment groups. The two-sided test for a difference between the interventions CRRT with CytoSorb and CRRT without CytoSorb at significance level 5% will be based on the two-sided 95% confidence interval from the linear regression model. This is expected to increase the power compared to a t-test, due to adjustment for baseline bilirubin level. The same modeling approach will be employed for the comparisons of CRRT without CytoSorb versus no CRRT and CRRT with CytoSorb versus no CRRT, respectively.

No interim analysis will be performed for the primary endpoint. Before the end of the study and enrollment of all participants, no early confirmatory conclusion of the superior efficacy of the study intervention can be drawn.

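### The plan rules out interim analysis, yet schedules about ten unblinded reviews of results that may stop the trial for benefit, with no endpoint or boundary

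*Protocol article*

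**What the plan says.** Two sections exclude interim looks. Protocol article, Statistical methods for analyzing primary and secondary outcomes: "No interim analysis will be performed for the primary endpoint". The next sentence there bars any confirmatory conclusion of superior efficacy before the study has ended with all participants enrolled. Data monitoring also says that no interim analysis is planned, giving the small sample as the reason, and does not restrict this to the primary endpoint.

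Two sections provide for them.
- Early termination of the study: "After inclusion of every fifth patient, the principal investigator, the co-principal investigators, and the trial statistician will discuss the risk-benefit ratio". The discussion rests on the results of the patients included so far and leads to a joint decision to continue or discontinue. The list of termination criteria in the same section includes early "evidence of benefit or harm of the experimental" intervention.
- Data monitoring: on "premature evidence of the inferiority of the control group, the study can be interrupted at any time".

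No endpoint, threshold or alpha is given for these decisions. The trial is open-label for the study team as well (Blinding), the team has full access to all data (Access to data), and Data monitoring states that no data monitoring committee is required.

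**The concern.** A scheduled look at accumulating results that can end the trial for benefit is an interim analysis, whatever it is called. With 51 patients and a review after every fifth, there are ten such looks (at 5, 10, ..., 50) before the final analysis. The people looking know the allocation, and bilirubin is in the patient chart.

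The plan does not say what becomes of the primary test after a benefit stop, so two readings are open. On one, the test is still reported as confirmatory, and repeated looks raise the error. On the other, the bar on early confirmatory conclusions applies, and a benefit stop forfeits the answer to the trial's only confirmatory question. On both, stopping when the difference looks large biases the estimate and its 95% confidence interval, which the plan says it will emphasise over p values.

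**Working it through.** **1. The plan's own figure.** Inputs from Sample size: "two-sided significance level of 5%, a sample size of 17 patients in each group yields a power of 80"%, where "the mean serum bilirubin levels after 72 h differ by 5 mg/dl, given a standard deviation of 5 mg/dl in both groups". The standardised effect is 5/5 = 1.0. The two-sample t-test has noncentrality 1.0 × √(17/2) = 2.92 on 32 degrees of freedom. The exact calculation needs n = 16.71, so 17 per arm, with power 80.7%. The figure reproduces. It describes one fixed-sample test with no allowance for looks.

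**2. Number of looks.** 51/5 = 10.2, so there are ten reviews plus the final analysis at 51.

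**3. Simulation inputs.**
- From the plan: "Allocation to the intervention and control groups is carried out by 1:1:1 randomization, stratified for baseline serum bilirubin level"; 17 per arm; SD 5; no missing values ("No missing values up to 72 h are expected").
- Assumed, because the plan gives nothing: block lengths 3 or 6; at least 3 patients in each of the two CRRT arms before a look counts; 72 h bilirubin available at each look; a stop when the comparison of CRRT with and without CytoSorb reaches a given p value.
- Statistic at each look: t = (difference in means)/(s·√(1/n₁ + 1/n₀)). 20,000 trials per setting.

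**4. No true effect, primary test still claimed after a stop.**

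| p value that stops the trial | Stop in either direction | Stop for benefit only |
|---|---|---|
| <0.05 | about 18% | 11–12% |
| <0.01 | 7–8% | about 7% |
| <0.001 | about 5% | about 5% |

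Requiring five patients per arm lowers the first row to about 15% and 10%. The planned analysis is a baseline-adjusted regression with robust standard errors of unstated type. With an assumed baseline correlation of 0.5, the first row becomes 19.5% and 12.3% with HC2 errors, and 13.0% and 8.5% with HC3.

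**5. No true effect, bar applied strictly.** A confirmatory claim then requires that the trial was not stopped and that the test at 51 is significant. This is a subset of the fixed-sample rejections, so the error cannot exceed that of the final test. With benefit stops at p<0.05 it is about 2.7%. Stopping for harm alone gives about 2.5%.

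**6. Planned effect of 5 mg/dl, stops for benefit.**

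| p value that stops the trial | Stopped early | Confirmatory result under the strict bar | Mean estimate at stop (mg/dl) |
|---|---|---|---|
| <0.05 | 86% | about 1% | 6.3–6.7 |
| <0.01 | 64% | about 18% | 6.9–7.1 |
| <0.001 | 32% | about 49% | 7.6–7.7 |

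The ranges in the last column cover a minimum of 3 or 5 patients per arm. Without stopping, the chance of a confirmatory result is about 80% and the mean estimate is 5.

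**The case against.** The strongest defence has three parts.

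First, a reader might infer that the 5% level is simply unprotected. The documents do not support that. The statistical methods section says no early confirmatory conclusion of superior efficacy can be drawn, and if this is followed the error stays at or below 5%. This part stands. It moves the cost to power, however, and it conflicts with listing benefit as a reason to stop.

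Second, the reviews are introduced as a safety measure, through the mortality signal in an earlier trial of the device and the risk-benefit ratio. Nothing says that bilirubin is tested at any look or that p<0.05 triggers a stop. This also stands, and it is why the figures are conditional on an assumed rule and not a property of the plan. But the results to be reviewed are not limited to safety data, benefit is named as a criterion, and the statistician takes part.

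Third, the exclusion in the statistical methods section covers only the primary endpoint, so a safety review is compatible with it. That is correct for that section, but the statement under Data monitoring is unrestricted.

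Two further inferences should not be drawn. The exaggerated bilirubin estimate does not feed the sample size of the planned multi-center trial, because the plan uses survival time for that. Nor is the possible expansion of enrolment driven by efficacy: Sample size ties it to deaths before 72 h and to an amendment, and amendments need ethics approval.

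**Conclusion.** The contradiction is in the text and does not depend on any simulation: two sections exclude interim analysis, while the plan schedules about ten unblinded reviews and allows stopping for benefit or for inferiority of the control group, without endpoint, boundary or alpha.

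Its size depends on how a stop would be triggered and reported, which the plan leaves open. Either the error can rise above 5%, by an amount that is negligible at p<0.001 and large at p<0.05, or the error is held and a benefit stop costs most of the planned power. The exaggerated estimate follows on either reading. These figures assume a t-test rule and 72 h results available at each look. This should be fixed, but it does not show that the primary test as written exceeds its 5% level.

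**What to change.** Reconcile Statistical methods, Data monitoring and Early termination of the study. The simplest way:
- Remove benefit from the list of termination criteria, and remove inferiority of the control group from Data monitoring.
- Limit the review after every fifth patient to deaths, serious adverse events and device deficiencies, with no summaries by arm of bilirubin or other efficacy results.
- Leave stopping for safety unchanged.

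Alternatively, if stopping for benefit is wanted, prespecify the endpoint and a strict efficacy boundary, say how the primary test and estimate are reported after a stop, and correct the statements that there is no interim analysis.

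The first option is a wording amendment with no change to sample size or data collection. Its cost is giving up the informal option to stop early for benefit.

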### Dissemination policy

The results of this study will be presented at symposia and conferences and published in scientific journals. Assistance of a professional writer for the scientific publication(s) is not intended but will not generally be rejected. Authorship eligibility will follow the recommendation provided by the International Committee of Medical Journal Editors:

http://www.icmje.org/recommendations/browse/roles-and-responsibilities/defining-the-role-of-authors-and-contributors.html

After completion of the trial, de-identified individual participant data that underlie the results reported in the publication of this trial will be made available for individual participant data meta-analysis to researchers who provide a methodologically sound proposal beginning 9 months and ending 36 months following article publication, if in compliance with data protection legislation. Proposals should be directed to the corresponding author; to gain access, data requestors will need to sign a data access agreement.

## Discussion

The randomized, controlled CYTOHEP study is designed to evaluate the use of extracorporeal hemoadsorption using the CytoSorb device in patients with acute-on-chronic liver failure. Even though the CytoSorb device is frequently being used for the treatment of patients with liver failure, there is only limited evidence supporting this approach. Pre-clinical studies and retrospective patient data analyses suggest technical efficiency of the CytoSorb in reducing elevated levels of bilirubin and IL-6. Both parameters occur in excess in the patients’ blood in acutely decompensated liver cirrhosis. However, currently, there is no reliable evidence about the effect on patient-centered outcomes, including survival. The aim of the CYTOHEP study is to close this gap and provide evidence for or against the use of hemoadsorption with the CytoSorb device for these patients. To assess a potential effect of renal replacement therapy on the outcome of the patients, we also included a third group into this trial not receiving renal replacement therapy or CytoSorb. The controlled design of this study will allow to independently assess the effect of CytoSorb and renal replacement therapy on laboratory parameters and patient outcome. The single-center design will guarantee comparable standards for ICU treatment in all three arms of this trial.

## Data Availability

For the planning of this study and writing of the manuscript no specific primary data was collected. After completion of the trial, de-identified individual participant data that underlie the results reported in the publication of this trial will be made available for individual participant data meta-analysis to researchers who provide a methodologically sound proposal beginning 9 months and ending 36 months following article publication, if in compliance with data protection legislation. Proposals should be directed to the corresponding author; to gain access, data requestors will need to sign a data access agreement.

